**Protocol Date: 2001-05-07**

**[name]**

**Protocol amendments:**

**December 12, 2006, Approved by the EPN**

***Overall Aim***

To optimize the routine for IUC insertion after medical abortion in order to reduce the number of consultations involved and to improve post abortion contraceptive use.

***Scientific background***

The introduction of medical abortion has changed abortion practices dramatically in several countries. Given the choice, a majority of women choose medical rather than surgical abortion(www.socialstyrelsen.se,1, 2). In Europe and globally a large proportion of abortions are repeat abortions (www.socialstyrelsen.se. 1. 2) . Intrauterine contraceptives (IUC) have been shown to be highly effective to prevent unwanted pregnancy.

Ovulation may return as early as eight to ten days after an induced abortion with no difference between medical and surgical abortion and 83% have ovulation during the first cycle after abortion(3).

To reduce the risk of a new unwanted pregnancy after surgical abortion, the IUC is inserted immediately after surgical first-trimester abortion, with well documented safety and efficacy (5). In some studies a somewhat higher expulsion rate was observed after immediate insertion compared to delayed insertion (6). This was however compensated for by the fact that all women got the IUC in the immediate insertion group, whereas the 42% of women scheduled for delayed insertion did not return. Furthermore, women were more likely to use an intrauterine contraceptive after six months if they had it inserted right away compared to some weeks after the abortion.

A disadvantage with medical abortion is the delayed insertion of IUC compared with surgical abortion. After medical abortion, the common routine is to wait 3-4 weeks or until the first post abortion menstruation until insertion of an IUC which means an obvious risk of a new pregnancy. This practice may also discourage women from IUC use due to the need for several follow up visits particularly in settings where women travel far distances for abortion care or where services are poor or expensive for women.

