***Outcome measures***

**Primary outcome**

Expulsion rates at 6 months after IUC insertion.

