**Allocation and treatment**

Designated study nurses and doctors will be responsible for recruiting and examining study participants at the outpatient clinic. Eligible women with a pregnancy up to 63 days gestation who elect to participate in the study and who sign an informed consent form will be randomised into either :

Group 1 (early IUC insertion on day 5-9 after mifepristone)

or

Group 2 (outpatient standard follow-up and IUC insertion at 3-4 weeks after mifepristone) .

Study participants will be administered mifepristone and misoprostol according to routine. All women will be screened for bacterial vaginosis and Chlamydia infection, and treated if positive but not excluded from participation. Women will receive mifepristone (Mifegyne®, Exelgyn, Paris, France) 200 mg orally at the clinic. The day when mifepristone is administered counts as Day one. Thirty-six to 48 hours later women self administered 800 mcg misoprostol vaginally (Four tbl Cytotec® 200 mcg, Pfizer, New York, USA).

An ultrasound examination will be performed prior to insertion of the IUC, and the anterior-posterior thickness of the endometrium recorded as well as the presence of any remaining products of conception. Women diagnosed with a continuing pregnancy or a missed miscarriage, or with any surgical intervention or untreated genital infection after the abortion treatment will excluded from the trial.

Intensity of pain will be recorded on the visual analogue scale (VAS) ranging from zero to ten (worst possible pain) directly after IUC insertion before any use of analgesia.

Serum hemoglobin (S-Hb) and serum human chorion gonadotropin (S-hCG) will be determined on treatment day one (the day of mifepristone administration), on the day of IUC insertion, and at four weeks follow up.

The patients will be scheduled to return for a follow-up visit four weeks after the IUC insertion. Any complications such as genital infection, and expulsion will be recorded.

Women will be advised to keep daily records (starting on day one) on the bleeding pattern and notes of any adverse events as well as any concomitant medication. Intensity of bleeding will be reported in relation to the individual woman's normal menstrual bleeding on a scale from sparse (much less than menstrual bleeding) to heavy (much heavier than menstrual bleeding).

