**Randomization procedure**

Women who volunteer to participate in the study will be assigned, within each stratum (Cu-IUD or LNG-IUS), to either group at a ratio of 1:1 using a computer generated randomization list. The randomisation procedure is a third party concealed randomisation. A study nurse, not directly involved in the study, will perform block randomisation, 10 subjects to each block, and create opaque, numbered, envelopes containing the randomisation group for each participant. Randomisation will occur upon opening the envelope consecutively after the participant has signed informed consent to participate.

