***Statistical analysis; power calculations - sample size***

***Sample size***

The main outcome of the study is to detect any difference in expulsion rate between women assigned to the early and the delayed IUC insertion groups. Since no data on expulsion rates of IUC after early post medical insertion is available at the time of the study start we assumed that expulsion rate after early insertion post medical abortion is similar to the expulsion rate after immediate insertion post surgical abortion. In a previous study of immediate IUC insertion post surgical abortion, the expulsion rate during the first year was found to be 15,4 % in the immediate group compared to 2,8% in the delayed insertion group (6). With 60 patients in each randomized group we will have a power of 78% in a one-sided test (alpha-level: 5%) to detect a difference between the groups of the same magnitude as in the study by Gillett et al. To evaluate the differences between the groups regarding independent nominal data such as expulsion, side-effects and compliance, the chi squared test will be used. Continuous variables with a normal distribution, such as age will presented as medians (range) and compared using Mann-Whitney U-test. Also discrete numerical variables such as parity and bleeding patterns will be presented as medians (range) and assessed for normality and comparison using the Mann-Whitney U-test. Results will be considered statistically significant if P-value < 0·05.

The data will be analysed using the intention-to-treat principle, including all women in the groups as randomized. Numbers and proportions of women receiving IUC insertion will be calculated by intervention. Both interventions will be compared using both absolute and relative measures with 95% confidence intervals.

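### The 78% power treats all 60 randomised women per arm as inserted and evaluable; for an expulsion rate after insertion it is an upper bound

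*Protocol*

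**What the plan says.** The sample-size paragraph of the protocol (Statistical analysis; power calculations - sample size) states: "With 60 patients in each randomized group we will have a power of 78% in a one-sided test (alpha-level: 5" per cent). The planning rates come from a study of insertion after surgical abortion: "15,4 % in the immediate group compared to 2,8% in the delayed insertion group (6"). The paragraph mentions no allowance for women who are not inserted, are excluded, withdraw or are lost.

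Other sections bear on how many women can contribute:

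- Primary outcome: "Expulsion rates at 6 months after IUC insertion".
- Randomization procedure: allocation is 1:1, and "Randomisation will occur upon opening the envelope consecutively after the participant has signed informed consent to participate". Insertion follows days later in the early group and weeks later in the delayed group.
- Allocation and treatment: at the ultrasound before insertion, women with a continuing pregnancy or missed miscarriage, or "with any surgical intervention or untreated genital infection after the abortion treatment will excluded from the trial".
- Discontinuation: women may withdraw after recruitment.
- Scientific background, on insertion after surgical abortion: every woman in the immediate group received the device, "whereas the 42% of women scheduled for delayed insertion did not return".

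The sample-size section also promises an intention-to-treat analysis of every woman in her allocated group.

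**The concern.** The number randomised and the number that the power formula needs with a result are the same, 60. An expulsion can occur only in a woman who has received a device, and the 6-month status must be known. Between randomisation and that point the design has several exits: no insertion, exclusion at the insertion visit, withdrawal, and failure to reach the woman by telephone at 6 months. The rate of insertion is itself a secondary outcome, and the background says that delay may put women off, so unequal insertion between the arms is part of the reason for the trial. The power statement sets all of this to zero.

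At stake is how a non-significant expulsion result would be read. A reader would take it that the planned difference had a 22% chance of being missed. With fewer evaluable women that chance is larger.

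**Working it through.** **Inputs from the protocol.** Expulsion p1 = 0.154 (early) and p2 = 0.028 (delayed); one-sided alpha 0.05, z = 1.645; 60 per arm, 1:1; chi-squared test. The protocol gives no rate for exclusion, withdrawal or loss in this trial, so the loss rates below are assumptions. The exception is 42%, which is cited from surgical abortion.

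**Formula** (pooled two-proportion normal approximation, n1 early and n2 delayed evaluable women):

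- p̄ = (n1·p1 + n2·p2)/(n1 + n2)
- s0 = √[p̄(1 − p̄)(1/n1 + 1/n2)]
- s1 = √[p1(1 − p1)/n1 + p2(1 − p2)/n2]
- power = Φ[(p1 − p2 − 1.645·s0)/s1]

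**Step 1: reproduce the stated figure.** With n1 = n2 = 60: p̄ = 0.091, s0 = 0.0525, s1 = 0.0512. Power = Φ[(0.126 − 1.645 × 0.0525)/0.0512] = Φ(0.77) = 78.0%. Solving the other way for 78% returns 60 per arm. The published arithmetic is right, and it contains no margin for loss.

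**Step 2: same formula, fewer evaluable women.**

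| Assumed loss (early / delayed) | Evaluable (early / delayed) | One-sided power |
|---|---|---|
| none | 60 / 60 | 78.0% |
| 5% / 5% | 57 / 57 | 76.2% |
| 10% / 10% | 54 / 54 | 74.1% |
| 5% / 25% | 57 / 45 | 70.1% |
| 0% / 10% | 60 / 54 | 75.6% |
| 0% / 25% | 60 / 45 | 70.7% |
| 0% / 42% | 60 / 35 | 62.7% |

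The last row uses 60 × (1 − 0.42) = 34.8, rounded to 35: p̄ = 0.1076, s0 = 0.0659, s1 = 0.0543, and Φ(0.32) = 62.7%. The chance of missing the planned difference goes from 22% to 37%.

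**Step 3: dependence on the method.** Other one-sided calculations start at a different level, and all fall between 60/60 and 60/35: unpooled normal 79.2% to 75.0%, arcsine 82.4% to 71.4%, uncorrected chi-squared by exact enumeration 82.8% to 69.2%, Fisher's exact test 72.1% to 50.1%. The direction does not depend on the method; the size does. The pooled formula is used above because it returns the protocol's own 78%.

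**Step 4: the other denominator.** Suppose women without an insertion stay in the denominator as non-expulsions. At 42% delayed non-insertion the delayed rate becomes 0.028 × 0.58 = 0.016, and with 60 per arm the power is 86%. At 5% early and 25% delayed non-insertion the rates are 0.154 × 0.95 = 0.146 and 0.028 × 0.75 = 0.021, and the power is 80%. At 10% in both arms it is 74%.

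**The case against.** The strongest reply is that the protocol commits to analysing all women as randomised. On that basis a reader who infers that 78% cannot be reached goes too far: step 4 shows nominal power of 80% to 86% when non-insertion falls mainly on the delayed arm. That stands, and it rules out an unconditional claim. It does not rescue the power statement for the outcome as named. The gain comes from counting women who never had a device as successes, so the contrast mixes non-insertion with expulsion and is no longer an expulsion rate after insertion. An all-randomised denominator also sits uneasily with the exclusions made at the insertion visit.

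A second reply is that 42% is not a planning value. That is correct. A reader might infer that the protocol expects 42% non-insertion in its own delayed arm, but the figure is background from surgical abortion and no section states an expected rate for this trial. It serves only as an extreme.

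Third, with modest equal losses the shortfall is 2 to 4 points, small beside the uncertainty of planning rates borrowed from surgical abortion. This is fair, and it limits the weight of the point.

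Fourth, 60 might mean 60 women inserted. The wording, which refers to each randomised group, makes that less natural, but one sentence could settle it.

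**Conclusion.** The point holds in a limited form. At the planned rates and by the formula that reproduces it, 78% requires all 60 randomised women in each arm to have an IUC inserted and a 6-month expulsion result. If inserted, evaluable women form the denominator, 78% is an upper bound: about 76% to 74% with 5% to 10% loss in both arms, 70% with 5% early and 25% delayed loss, and 63% in the illustrative extreme. These loss rates are assumptions.

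This is an omitted allowance and not a miscalculation. The documents do not support saying that the power is unattainable under every analysis, that 42% is the expected loss, or that the trial must be larger. Nor does the point rest on how the analysis plan, which is not at hand, treats missing data: it concerns a figure that the protocol itself states.

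**What to change.** In the sample-size paragraph, restate the power for the expected number of inserted and evaluable women per arm over a stated range of loss. For loss in the delayed arm only, 10%, 25% and 42% give about 76%, 71% and 63% (60/54, 60/45 and 60/35). The 42% should be labelled as taken from surgical abortion. Alternatively, state that 60 per arm means 60 women with an IUC inserted and followed to 6 months, if that was the intention; more than 60 per arm would then have to be randomised whenever any loss occurs. The Scientific background needs no change.

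The cost is a sentence or two. Restating the figure requires no increase in sample size and no change to conduct; the stated power becomes less favourable.

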***Objectives***

The objective of the present study is to compare early versus delayed IUC insertion post medical abortion with regard to risk of expulsion, rates of insertion, bleeding patterns and complications, including both the common types of modern IUC, the T shaped Cu-IUD and the LNG-IUS, up to 6 months following IUC insertion.

***Design***

Prospective randomised controlled trial

***Setting/Centres***

The Department of Obstetrics and Gynaecology, Karolinska University Hospital/ Karolinska Institutet, Stockholm, Sweden.

***Participants***

Women requesting medical termination of pregnancy with pregnancies up to 63 days gestation (based on ultrasound) and opting for post abortion IUC.

***Interventions***

Women with an unwanted pregnancy up to 63 days gestation, who request medical abortion, and opt for post abortion IUC will be randomised into two groups:

Group 1) IUC insertion 5 to 9 days after mifepristone administration.

Group 2) IUC insertion according to the clinical routine 3-4 weeks after mifepristone administration.

Follow up will be done at 4 weeks, 3 months and 6 months after IUC insertion.

***Outcome measures***

**Primary outcome**

Expulsion rates at 6 months after IUC insertion.

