Women will be contacted by telephone at 3 and 6 months after the IUC insertion and asked to answer a questionnaire about pregnancy, expulsion, bleeding patterns, pelvic pain, pelvic infections, continuous use and overall satisfaction with the contraceptive method.

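### Expulsion is counted from IUC insertion, but the only analysis rule counts all randomised women, so the denominator is unsettled and never-inserted women have no scheduled follow-up

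*Protocol*

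**What the plan says.** The primary outcome (Protocol, Primary outcome) is "Expulsion rates at 6 months after IUC insertion". Its clock starts at an event that comes after allocation: under Randomization procedure, "Randomisation will occur upon opening the envelope consecutively after the participant has signed informed consent to participate".

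The analysis rule (Protocol, Sample size) is "The data will be analysed using the intention-to-treat principle, including all women in the groups as randomized". It makes no exception for any outcome. For the test, the same section says that "regarding independent nominal data such as expulsion, side-effects and compliance, the chi squared test will be used".

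Follow-up is also tied to insertion. The Interventions section counts the 4-week, 3-month and 6-month follow-up from insertion, and the telephone follow-up text says "Women will be contacted by telephone at 3 and 6 months after the IUC insertion". Those calls ask about pregnancy, expulsion and continued use.

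Three other statements bear on the point:
- Scientific background reports earlier surgical-abortion data in which every woman in the immediate group received the IUC, "whereas the 42% of women scheduled for delayed insertion did not return".
- Overall Aim includes the purpose "to reduce the number of consultations involved and to improve post abortion contraceptive use".
- Insertion rate is a secondary outcome, and the Sample size section plans to report it by arm.

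**The concern.** A woman who never receives an IUC has no time zero for the primary outcome and cannot expel a device. The protocol does not say how she enters the primary comparison. There are two readings:

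- **All randomised women in the denominator.** She counts as not expelled, so failing to insert lowers an arm's expulsion rate.
- **Only inserted women in the denominator.** The rate has a clear meaning, but the analysis departs from the stated rule and compares groups formed after randomisation.

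The protocol's own background makes unequal non-insertion foreseeable, with more of it in the delayed arm. At stake is a finding against early insertion that partly reflects women in the delayed arm not coming back.

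The second problem is in data collection. A never-inserted woman has no date from which a 3- or 6-month call can be set, so her pregnancy and contraceptive use are not collected. No later analysis plan can recover data that were never gathered.

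**Working it through.** **Inputs from the protocol (Sample size):** 60 women per randomised group; planning expulsion rates 15.4% early and 2.8% delayed; one-sided 5% test; stated power 78%. From Scientific background: 42% non-return for delayed insertion, against full insertion in the immediate group.

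**Assumptions, not in the protocol:** the delayed non-insertion share m in this trial (10%, 20% and 42% are used, with none in the early arm, plus one case of 95% vs 75% inserted); an equal true per-insertion risk of 10% for the false-positive check; and non-insertion unrelated to a woman's expulsion risk.

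**Step 1. Reproduce the stated power.** For two proportions with pooled variance under the null:

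power = Φ[(p1 − p2 − 1.645 × SE0) / SE1]

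Here p1 = 0.154, p2 = 0.028 and the pooled rate is 0.091.
- SE0 = √(2 × 0.091 × 0.909 / 60) = 0.0525
- SE1 = √(0.154 × 0.846/60 + 0.028 × 0.972/60) = 0.0512
- Power = Φ[(0.126 − 0.0864)/0.0512] = 78.0%, which agrees with the protocol.

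This calculation treats all 60 women per arm as at risk of expulsion; no allowance for non-insertion is stated.

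**Step 2. Planning rates, all randomised women in the denominator.** The delayed rate becomes 0.028 × (1 − m).

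| m | Delayed rate | Difference (points) | Risk ratio |
|---|---|---|---|
| 0 | 2.8% | 12.6 | 5.5 |
| 10% | 2.5% | 12.9 | 6.1 |
| 20% | 2.2% | 13.2 | 6.9 |
| 42% | 1.6% | 13.8 | 9.5 |

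The absolute shift is at most 2.8 − 1.6 = 1.2 points, though the risk ratio moves a good deal.

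**Step 3. No true difference per insertion (10% in both arms).** The all-randomised rate in each arm is 0.10 × (share inserted). Rejection probabilities come from exact binomial enumeration of the uncorrected chi-squared test, 60 per arm. The one-sided test is in the direction of more expulsion with early insertion.

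| Inserted, early vs delayed | Rates compared | One-sided | Two-sided |
|---|---|---|---|
| 100% vs 100% | 10.0% vs 10.0% | 5.1% | 5.0% |
| 100% vs 90% | 10.0% vs 9.0% | 7.4% | 5.4% |
| 95% vs 75% | 9.5% vs 7.5% | 10.9% | 6.7% |
| 100% vs 58% | 10.0% vs 5.8% | 22.2% | 13.3% |

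Both columns matter: the power statement is one-sided, while the analysis text names a chi-squared test at P < 0.05.

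**Step 4. Inserted women only.** Early n = 60; delayed n = 60 × (1 − m); planning rates unchanged; same formula as Step 1. One-sided power is 75.6%, 72.5% and 62.5% at m = 10%, 20% and 42%, against the stated 78%.

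**Step 5. IUC in place at 6 months, all randomised women.** Only non-insertion and expulsion are counted as loss, using the planning rates. Early: 1 − 0.154 = 84.6%. Delayed: (1 − m) × 0.972 = 87.5%, 77.8% and 56.4% at m = 10%, 20% and 42%. The arms are equal at m = 1 − 0.846/0.972 = 13%. Above that, early insertion has more expulsion but leaves more women with an IUC.

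**The case against.** The case on the other side has weight, and several stronger readings should be set aside.

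- A reader might infer that the protocol orders never-inserted women to be scored as not expelled. It does not; that is the consequence of applying the all-women rule literally to a yes/no outcome. The outcome's own wording, counted from insertion, points towards inserted women as the group at risk. The protocol also excludes some women at the pre-insertion assessment, so not every non-insertion would be scored as a success. What stands is that neither reading is stated and they give different results.
- A reader might infer that no all-randomised outcome captures the benefit of early insertion. Insertion rate by arm is planned, with absolute and relative measures and confidence intervals, and it captures part of that benefit.
- A reader might infer that IUC use in all randomised women cannot be computed. It can be approximated by counting the never-inserted as non-users, apart from a time-origin shift of about two to three weeks between the arms. What is truly missing for these women is pregnancy, an IUC obtained later or elsewhere, and other contraceptive use.
- A reader might infer that the bias is necessarily large. The 42% comes from surgical abortion, and the protocol assumes no rate for this trial. At modest non-insertion the two-sided inflation is slight (5.4% and 6.7% in Step 3).

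It can also be said that denominators are often left to the analysis plan. That would answer a gap, but here the protocol states one general rule that does not fit its primary outcome. The contact schedule lies outside what an analysis plan can repair.

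**Conclusion.** The point holds as a conflict between stated parts of the protocol and should be fixed. Under the literal rule, the arm with more non-insertion looks better on expulsion. That this would be the delayed arm is supported, but not established, by the surgical background data.

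At equal 10% risk per insertion, false rejection runs from about 7% one-sided and 5.4% two-sided at 10% delayed non-insertion to 22% and 13% at 42%. These figures rest on the assumed non-insertion rates and common risk. If the planning rates are right, the primary difference changes by at most 1.2 points and the direction of the conclusion does not change.

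The loss of pregnancy and later contraceptive data for never-inserted women follows directly from the contact schedule, whatever rate is assumed, and it bears on the stated overall aim.

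**What to change.** 1. State that expulsion is analysed among women with an IUC inserted, grouped by randomised arm. Label this as a non-ITT comparison and exempt it from the all-women denominator.
2. Add, as a secondary ITT outcome, IUC in place at 6 months after mifepristone in all randomised women. Count the never-inserted as non-users unless an IUC obtained elsewhere is reported.
3. For women without an insertion, time the 3- and 6-month telephone contacts from mifepristone.

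The cost is a few sentences of protocol text, one more secondary outcome and two telephone calls per non-inserted woman. The inserted-women comparison also gives up the full protection of randomisation, which is why it needs its label. It loses power as well if many women are not inserted (Step 4). Keeping 60 inserted women in the delayed arm would take 60/(1 − m), that is 67, 75 or 104 randomised per arm at 10%, 20% or 42% non-insertion.
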